# The effects of dietary instruction on cardiovascular risk markers after smoking cessation: study protocol for a multicenter randomized controlled trial in Japan

**DOI:** 10.1186/s13063-018-2919-6

**Published:** 2018-10-04

**Keywords:** Smoking cessation, Weight gain, Obesity, Nutritional guidance, Cardiovascular risk, Adiponectin

## Abstract

**Background:**

Weight gain frequently occurs after smoking cessation (SC); the risk of new-onset diabetes mellitus increases for several years after SC. However, no large-scale, randomized controlled trials have examined the effects of nutritional guidance on post-SC cardiovascular risk. The current trial will enroll individuals who successfully quit smoking with the help of a SC clinic and who gain weight, to determine the effects of nutritional guidance on cardiovascular, glucose, and lipid metabolism biomarkers.

**Methods/design:**

This is a multicenter, prospective, parallel-group, randomized controlled trial. Some 250 individuals who successfully quit smoking with the help of a SC clinic and who gain weight (an increase of ≥ 1.25% Body Mass Index (BMI) between the first and the fifth visit to the SC clinic) will be enrolled within 1 month of the final (fifth) visit to the SC clinic. These participants will be randomly assigned to an intervention group (125 individuals receiving nutritional guidance) or a control group (125 individuals not receiving nutritional guidance). A registered dietitian will provide nutritional guidance once every 3 months for a total of three sessions. The primary endpoint for this trial will be the level of adiponectin, a predictor of cardiovascular risk that reflects weight and smoking status. Secondary endpoints will be levels of cardiovascular, glucose, and lipid metabolism biomarkers, BMI, abdominal circumference, and the percentage of individuals who quit smoking for a prolonged period.

**Discussion:**

This trial will determine the benefits of nutritional guidance with respect to post-SC weight gain. The findings should provide useful information for devising a quality protocol for SC education to prevent cardiovascular disease.

**Trial registration:**

The study is registered at the University Hospital Medical Information Network Clinical Trials Registry (UMIN000030282). Registered on 6 December 2017.

**Electronic supplementary material:**

The online version of this article (10.1186/s13063-018-2919-6) contains supplementary material, which is available to authorized users.

## Background

### Effects of smoking

Smoking contributes to the development of fatal cardiovascular diseases and malignancies. Worldwide, approximately 5.4 million people die from preventable smoking-related diseases each year; this number corresponds to 10% of all adults [1]. According to the Ministry of Health, Labor, and Welfare, heart disease is the second-leading cause of death in Japan, accounting for approximately one sixth of Japanese deaths [2]. National medical expenditures have exceeded 38 trillion yen, accounting for more than 10% of the national income. The greatest portion (21%), 5.8 trillion yen, is spent on cardiovascular disease. The Japan Collaborative Cohort Study involved 95,000 Japanese, and it found that smoking increased the risk of death from cardiovascular disease 1.6–2.0-fold, resulting in exorbitant medical expenditures [3]. Nonetheless, 30% of male adults and 10% of female adults in Japan smoke [4]. Japan has one of the highest smoking rates among developed countries, and smoking cessation (SC) must be promoted further.

### Weight gain after smoking cessation

Efforts to curb smoking should significantly decrease the development of cardiovascular disease and sharply curtail medical expenditures. However, individuals are known to gain weight after SC, making obesity prevention and subsequent medical expenditures a concern [5, 6]. The extent of weight gain varies depending on the study, but men who quit smoking on their own gain 2.8 kg on average, whereas women gain an average of 3.8 kg; 20–40% of people gain 13 kg or more [6]. Weight gain after SC can cause individuals to resume smoking, which increases cardiovascular risk. SC aids, such as nicotine patches or varenicline, help minimize weight gain after SC; nevertheless, individuals can gain weight for several years after SC despite receiving treatment. Weight gain frequently results in poorer glucose tolerance and a resumption of smoking. We have reported a case in which glucose tolerance significantly decreased with weight gain after SC [7]. The current authors have previously examined predictors associated with weight gain during SC treatment. Smokers with a high Fagerström Test for Nicotine Dependence (FTND) score upon an initial visit to a SC clinic (smokers with a high level of nicotine dependence) were more likely to gain weight after quitting smoking [8]. The advantages of SC are intricately combined with the disadvantages of post-SC weight gain. α1-antitrypsin low-density lipoprotein (AT-LDL) complex is an oxidatively modified LDL that promotes atherosclerosis. We had previously found that the level of AT-LDL in the blood is closely related to smoking status, that AT-LDL levels improve (decrease) 3 months after SC [9], and that cardiovascular markers do not improve in individuals who gain a substantial amount of weight after quitting smoking [10]. These findings suggest that post-SC weight gain might increase the risk cardiovascular events even though the individual quits smoking. This hypothesis is compatible with a study reporting no clear advantages of SC in diabetics who gain 5 kg or more [11]. In other words, preventing weight gain after quitting smoking could further reduce cardiovascular risk. Smoking and obesity are closely related, and they synergistically increase cardiovascular risk factors such as cerebral infarction and myocardial infarction. Promptly addressing this problem is vital in terms of medical and social costs.

### Standard smoking cessation treatment in Japan

SC treatment will be conducted according to the Standard Procedures for Anti-Smoking Treatment (originally issued in March 2006 by the Japanese Circulation Society, the Japan Lung Cancer Society, and the Japanese Cancer Association) [12]. SC treatment consists of using SC aids, such as nicotine patches or varenicline, along with nondrug therapy such as counseling from a physician or nurse. Smokers may continue to gain weight for 2–3 years after SC. However, there are no specific practice guidelines regarding minimizing weight gain after completing the 12-week SC treatment covered by the National Health Insurance. The standard procedures for anti-smoking treatment list weight gain as a possibility despite the use of SC aids; however, it does not list specific methods to deal with problem.

### Nutritional guidance for individuals who successfully quit smoking

Although diet is understood to affect obesity, appropriate dietary intake and a balanced diet for each individual are unclear, hampering obesity alleviation. Nutritional guidance allows a registered dietitian to review an individual’s diet in light of their energy expenditure and nutritional balance. It also helps the dietitian and individual to devise obesity prevention strategies and ameliorate illness, which has a substantial impact on medical economics. A study has reported that providing nutritional guidance to women who resume smoking due to fear of gaining weight helps inhibit post-SC obesity and increases the percentage of women who quit smoking for a prolonged period [13]. However, large-scale prospective, comparative trials have not yielded evidence for the effects of nutritional guidance on cardiovascular risk for every individual who is likely to gain weight after SC.

### Objective of this trial

The aim of this trial is to determine and compare the effectiveness with which nutritional guidance prevents obesity after SC, the effects of nutritional guidance on cardiovascular, glucose, and lipid metabolism biomarkers, and the effects of nutritional guidance on individuals who quit smoking for a prolonged period. This trial will involve individuals who successfully quit smoking with the help of a SC clinic and gained weight.

Inhibiting weight gain after SC will help maintain glucose tolerance and prevent new-onset diabetes mellitus. An altered body composition with increased visceral fat reduces glucose tolerance while promoting oxidative stress and inflammation. However, a previous study reported that weight gain due to SC increases not only fat but also bone and muscle tissues [14]. Adiponectin levels are closely and inversely correlated with the amount of visceral fat, and numerous studies have reported that decreased adiponectin levels are associated with decreased glucose tolerance. Furthermore, adiponectin levels decrease even when weight gain is inhibited by resuming smoking. Among the numerous markers and items studied, blood adiponectin levels are particularly closely associated with abdominal obesity, smoking, oxidative stress, and obesity- and smoking-associated inflammation. Thus, adiponectin is an optimal marker for use in our study, and we have selected it as the primary endpoint.

## Methods/design

### Design and sample size

This trial will be a multicenter, prospective, parallel-group randomized controlled trial. Participants will be assigned either to a group receiving nutritional guidance (once every 3 months) or to a group not receiving nutritional guidance. We chose 3-monthly visits because nutritional guidance typically continues for about 6 months. In addition, a previous study reported that frequent visits have a greater effect on weight gain and that follow-up is needed at least once every 3 months [15]. Participants will be enrolled for 3 years after the trial is approved by the Central Ethics Review Committee. The total duration of the trial will be 6 years (scheduled duration: April 2016 to March 2022).

Our target enrollment is 250 participants (125 individuals in the control group, 125 individuals in the intervention group). No similar clinical studies exist to serve as a reference. Although the exact sample size cannot be calculated, it has been estimated as follows:

In previous studies by our group, changes in adiponectin levels had served as the primary endpoint, and the standard deviation (SD) for changes in adiponectin levels (defined as the percentage of change in adiponectin levels before and after treatment, with the adiponectin level prior to treatment representing 100%) was 20%. We envision a similar approach for the current trial, and the SD is set at 20% to compare the percentage of change in adiponectin levels in the two groups (individuals who do not receive nutritional guidance vs. individuals who do). In order to detect a 10% difference between the assigned groups (effect size: 0.5) at a two-tailed alpha level of 5%, with a power of 80% and an adjustment for multiple primary endpoints, each group will need to consist of 82 individuals. Assuming a 25% drop-out rate during follow-up, based on data amassed from the SC clinic, 110 participants would need to be enrolled in each group. In light of the aforementioned estimates and other factors for error, the required enrollment would ultimately be a total of 250 individuals who visit the SC clinic, or approximately 125 individuals in each group.

The study’s inclusion and exclusion criteria are outlined in Table 1. The participants must meet all of the inclusion criteria and none of the exclusion criteria.

**Table 1 Tab1:** Inclusion and exclusion criteria

Inclusion criteria	
1. Individuals who successfully quit smoking* upon their fifth visit to the SC clinic;	
2. Within 1 month of an individual’s fifth visit to the SC clinic for SC treatment based on the standard protocol	
3. Individuals with ≥ 1.25% increase in BMI between their first and fifth visits to the SC clinic	
4. Individuals from 20 to 80 years of age when consent is obtained	
5. Individuals from whom consent has been obtained in writing	
Exclusion criteria	
1. Individuals regularly receiving nutritional guidance	
2. Individuals unlikely to benefit from nutritional guidance because of their general condition	
3. Individuals in shock, with a severe infection, in the acute stage of cerebral infarction or myocardial infarction, or with terminal-stage cancer	
4. Individuals with a BMI less than 18.5 (underweight)	
5. Individuals who are pregnant or nursing	
6. Individuals who are regularly receiving corticosteroids	
7. Individuals with poorly controlled diabetes mellitus (i.e., individuals with a HbA1c level consistently above 10.0% despite treatment)	
8. Individuals otherwise deemed ineligible by an investigator for participation in this trial (e.g., individuals with severe dementia or a poorly controlled psychiatric disorder) for reasons of participant safety or to ensure that the trial is conducted openly and fairly	

*BMI* Body Mass Index, *HbA1c* glycosylated hemoglobin, *SC* smoking cessation

* individuals who indicate in an interview that they have not smoked in the past week and have an exhaled carbon monoxide concentration of 7 ppm or lower

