### Observation and testing schedule

#### Primary endpoint

The primary endpoint for this trial will be the adiponectin level. Adiponectin is a peptide hormone secreted by adipocytes that inhibits atherosclerosis [17, 18]. Adiponectin is also a cardiovascular disease risk marker closely related to smoking, obesity, and atherosclerotic disease (i.e., adiponectin levels decrease as a result of smoking or obesity) [17, 18].

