#### Items analyzed and analytical methods

The participant characteristics in both groups will be described statistically. Mean values for weight, abdominal circumference, changes in marker levels for glucose and lipid metabolism, along with changes in cardiovascular biomarkers from enrollment until 9 months after enrollment, will be compared between the two groups. The distribution of individual indices at baseline and at 9 months after enrollment will be determined for the two groups, and a *t* test or a Wilcoxon rank-sum test will be performed. In addition, Fisher’s exact test will compare the percentage of individuals who quit smoking for a prolonged period in the two groups. The level of significance will be 0.05 or less. A two-tailed alpha of 5% and a two-sided 95% confidence interval will be used. The statistical analysis will be performed by a statistician. The primary endpoint will be assessed statistically to facilitate an interim analysis. Nutritional guidance will be deemed effective or ineffective in the final analysis using the statistic *Z*_prop_ = 1.567. An interim analysis will be performed after the 125 participants (an intermediate number of individuals out of the total enrollment) complete follow-up. This interim analysis will determine whether to terminate this trial for efficacy or futility. Trial termination for efficacy will be based on *Z*_prop_ > 2.538, whereas trial termination for futility will be based on *Z*_prop_ < 0.698.

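### The 82 per group rests on an adjustment for several primary endpoints, but the protocol defines one; the stated 80% is therefore not the power of the design described (about 89% at 82 per group in a fixed design)

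*Protocol article*

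**What the plan says.** The protocol article, under Design and sample size, takes the percentage change in adiponectin as the quantity to compare: "the SD is set at 20% to compare the percentage of change in adiponectin levels in the two groups". It aims at a difference of 10 (effect size 0.5) at a two-tailed 5% level, and reaches its size "with a power of 80% and an adjustment for multiple primary endpoints, each group will need to consist of 82 individuals". Neither the number of endpoints nor the method of adjustment is given. A 25% drop-out allowance raises 82 to 110 per group, and a further margin raises this to 125 per group, 250 in all.

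Elsewhere the primary endpoint is singular. Objective of this trial: "adiponectin is an optimal marker for use in our study, and we have selected it as the primary endpoint". Primary endpoint: "The primary endpoint for this trial will be the adiponectin level". The Abstract and the Discussion say the same, and Secondary endpoints classes the other markers, the body measurements and prolonged abstinence as secondary. Items analyzed and analytical methods also has one primary endpoint in view ("The primary endpoint will be assessed statistically to facilitate an interim analysis") and describes no correction for several primary endpoints.

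**The concern.** The sample-size paragraph relies on a design feature that the endpoint and analysis sections do not contain. If the adjustment belongs, primary endpoints are missing from the protocol, and so is the rule for declaring success on them. If it does not belong, the stated 82 and 80% do not go together for this trial. A reader cannot tell which. The number of patients needed and the power claimed are figures on which funders, ethics committees and later readers rely, so they should match the trial described.

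**Working it through.** **Inputs** (Design and sample size): difference δ = 10, SD σ = 20, so d = 0.5; two-tailed α = 0.05; power 80%; 1:1 allocation; drop-out 25%. Number of primary endpoints: one (Primary endpoint; Objective of this trial).

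**Formula** (normal approximation, per group): n = 2σ²(z₁₋α/₂ + z₀.₈₀)²/δ² = 8 × (z₁₋α/₂ + 0.842)². The t-test sizes use the noncentral t distribution with the same inputs.

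**Step 1. One endpoint, as the protocol defines it.** 8 × (1.960 + 0.842)² = 62.8, so 63 per group. The t test gives 63.8, so 64. The plan's 82 does not follow without an adjustment.

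**Step 2. Can 82 be reached by assuming more endpoints?** The method is not stated, so each row is an assumption.

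| Assumed adjustment | Per group |
|---|---|
| Two endpoints, Bonferroni (α = 0.025) | 77 normal, 78 t test |
| The same, inflated for a Wilcoxon test | 78/0.955 = 81.7, so 82 |
| Two co-primary endpoints, both required, each d = 0.5 | 83 if independent; 82 at correlation 0.1 to 0.2 |
| Three endpoints, Bonferroni (α = 0.0167) | 84 normal, 86 t test |
| Four endpoints, Bonferroni | 90 normal, 91 t test |

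Worked values:
- Three endpoints, normal formula: 8 × (2.394 + 0.842)² = 83.8.
- Two independent co-primary endpoints: each needs power √0.80 = 0.894, so 8 × (1.960 + 1.250)² = 82.4.

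Several ordinary routes come to 82 or within two patients of it. All need two or three primary endpoints. They also imply different success rules: any one endpoint sufficing, or both required.

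**Step 3. Drop-out.** 82/0.75 = 109.3, so 110 per group. The plan's figure reproduces. For comparison, 64/0.75 = 85.3, so 86.

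**Step 4. Power for one endpoint, two-tailed 5%, no interim look.** Power ≈ Φ(0.5 × √(n/2) − 1.960).
- n = 82: Φ(3.202 − 1.960) = 89.3%; t test 88.9%.
- 250 enrolled: 125 × 0.75 = 93.75 evaluable per group. n = 93: Φ(3.410 − 1.960) = 92.6%. n = 94: Φ(3.428 − 1.960) = 92.9%; t test 92.6%.

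These are fixed-design figures. The protocol plans one interim analysis with efficacy and futility stops, and the sample-size paragraph does not mention it. The power actually achieved depends on the boundaries finally used.

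**The case against.** The strongest reply is that the arithmetic may be sound on its own terms. The analysis section allows a t test or a Wilcoxon test, and two Bonferroni endpoints with a Wilcoxon inflation give exactly 82. This stands. A reader might infer that 82 cannot be reproduced for any number of endpoints, but Step 2 shows otherwise. The conflict is with the endpoint definition, not within the calculation.

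A reader might also infer that the trial misses its 80% target. It does not. With the one endpoint defined, the target is exceeded, and the phrase itself causes neither loss of power nor inflation of the type I error.

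A third inference would be that the phrase leaves room to promote a secondary endpoint later. That is speculation: adiponectin is named alone in the Abstract, the Objective, the Primary endpoint section and the Discussion, and the other measures are listed as secondary.

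The authors also say that an exact size cannot be calculated, and they add a margin from 110 to 125 per group. So 250 does not hang closely on 82. This is a fair reason to leave enrollment alone, but it does not explain an adjustment for endpoints that the protocol lacks. Nor does condensation into an article: the phrase is a positive statement that other sections contradict. The full protocol may name a method, and for that reason the fix offers two routes.

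**Conclusion.** The point holds as an inconsistency between the sample-size paragraph and the endpoint definition. For the single primary endpoint, the stated inputs require 63 to 64 evaluable per group, so 82 is 18 to 19 per group more than the stated 80% needs. At 82 the power is about 89%, and at the planned 250 about 92 to 93%. The error is conservative.

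The figures assume the stated difference and SD, a two-sample comparison of means, 25% drop-out and no interim look. Which adjustment was meant cannot be determined from the article. The correction is worth making because the stated size and power should be those of the trial described, but the trial is not undersized on this account.

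**What to change.** Take one of two routes.

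1. **If adiponectin is the only primary endpoint:** delete the reference to an adjustment for multiple primary endpoints in Design and sample size. State that 64 evaluable per group give 80% power for a difference of 10 (SD 20) at two-tailed 5% in a fixed design, and that 250 enrolled with 25% drop-out leave about 93 to 94 per group, with about 92 to 93% fixed-design power. Add that the interim analysis changes these figures according to the boundaries finally used.
2. **If further primary endpoints were intended:** name them, the success rule and the adjustment method, consistently in Design and sample size, Primary endpoint, and Items analyzed and analytical methods.

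Keep enrollment at 250 in the first case. The cost is a text correction. The second route also calls for a matching change to the analysis section.

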### Discontinuation criteria

The trial treatment will be discontinued for participants in any of the following situations:

(1) a participant asks to withdraw their consent; (2) a participant has asked to stop receiving the trial treatment; (3) a participant’s underlying illness is exacerbated or recurs; (4) a participant’s underlying illness recurs or new cancerous lesions are noted; (5) a participant fails to make a visit as a result of a change in address or similar; (6) a participant dies; or (7) a participant is deemed ineligible for enrollment.

Participants who cease receiving the trial treatment will be followed and will receive routine care as drop-outs.

### Ethics approval

All procedures will be performed in accordance with the ethical standards of the Institutional and National Research Committees as well as the 1964 Helsinki Declaration and its later amendments or comparable ethical standards.

### Study protocol

An overview of the proposed study protocol can be found in Fig. 1. The schedule of enrollment, interventions, and assessments is shown in Fig. 2. The Standard Protocol Items: Recommendations for Interventional Trials (SPIRIT) Checklist is provided in Additional file 1.

**Fig. 1 Fig1:**
[figure not shown]
Overview of the study protocol

**Fig. 2 Fig2:**
[figure not shown]
Schedule of enrollment, interventions, and assessments

### Randomization

Prior to beginning this trial, the University Hospital Medical Information Network’s Internet Data and Information Center for Medical Research will be asked to create a central assignment system using the Electronic Data Capture (EDC) system. Once written consent is obtained from an individual who meets the inclusion criteria, and a lead investigator has verified that the individual meets all of the eligibility criteria and none of the exclusion criteria, the participant’s information will be registered in the EDC system. After registration, the EDC system will assign patient numbers that do not include the participant’s personal information. Immediately after entry, the EDC system will randomly assign the participants to one of two groups (the group receiving nutritional guidance or the group not receiving nutritional guidance) via dynamic allocation. A lead investigator (or study chair) and the study office of the Kyoto Medical Center will be notified of the patient numbers and the group assignments. Based on the EDC system assignment, a lead investigator will schedule nutritional guidance for individuals receiving nutritional guidance and a visit 9 months later for individuals not receiving nutritional guidance. Registration in the EDC system allows adjustments for confounding factors (age, sex, the FTND score, weight gain (kg) before and after SC, and the fear of gaining weight according to a survey) between groups. The participants will be randomized by minimization (a method of dynamic allocation).

